### Plasma Collection and Mechanistic Analysis

Plasma samples will be collected at baseline and after 6 months of medication. A 10-mL peripheral blood sample will be collected in ethylenediaminetetraacetic acid tubes, centrifuged at 1500*g* for 10 minutes, aliquoted, and stored at −80 °C until analysis. The phrase “phlegm-heat-toxin pathogenesis” refers to a TCM theoretical pattern characterized clinically by phlegm accumulation, heat-related symptoms, toxin-like pathogenic stagnation, and impaired qi regulation. In this trial, the concept will be operationalized using TCM symptom scores and exploratory plasma markers rather than treated as a directly observable biomedical entity. The exploratory biological analysis will evaluate whether YFSJ changes biomarker patterns associated with inflammatory activation, immune dysregulation, oxidative stress, ER stress, and bile-acid metabolism. Candidate assays include multiplex or enzyme-linked immunosorbent assay measurement of interleukin-6 (IL-6), IL-1-β, tumor necrosis factor-α, IL-8, interferon-γ, C-reactive protein, vascular endothelial growth factor, and other prespecified cytokines; targeted liquid chromatography-mass spectrometry or mass spectrometry analysis of bile-acid metabolites such as deoxycholic acid, taurochenodeoxycholic acid, and glycocholic acid; and validated assays for ER stress–related markers such as glucose-regulated protein 78 or binding immunoglobulin protein, CCAAT/enhancer-binding homologous protein, activating transcription factor 6, spliced X-box-binding protein 1, and related pathway proteins when measurable in plasma or extracellular vesicles. Untargeted metabolomics or proteomics may be used to generate hypotheses, with false discovery rate control for multiple testing.

### Adherence and Retention Strategies

Participants will receive phone reminders before scheduled visits. Participants who miss a visit will be contacted by phone, text message, or home visit, as appropriate, to determine the reason and encourage continued participation. Medication adherence will be assessed through returned packet counts and participant report. Available imaging, laboratory, and questionnaire data will be collected at withdrawal whenever consent permits.

### Data Management and Monitoring

Data will be recorded in standardized CRFs and entered into an EDC system. Research staff will receive uniform training in eligibility confirmation, informed consent, CT data collection, AI output recording, questionnaire administration, adverse event reporting, and data entry. Data queries will be resolved before the database lock. The sponsor and centralized clinical management team will perform regular internal monitoring to ensure participant safety, protocol adherence, and data quality.

Because the intervention is noninvasive and the risk is considered low, an independent data monitoring committee is not planned. Serious adverse events will be reported to the ethics committee and sponsor according to the protocol and regulatory timelines. Emergency unblinding will be allowed only when knowledge of the treatment assignment is essential for clinical management.

### Statistical Analysis

Data will be collected at baseline and during follow-up visits using standardized CRFs. Key data include demographics, clinical history, imaging findings (chest CT and AI-assessed nodule features), laboratory results (tumor markers, blood, urine, stool, liver and kidney function, and ECG tests), and patient-reported outcomes (TCM symptom scale, provided in Multimedia Appendix 1, HADS, and PSQI). To ensure data quality, assessors will receive uniform training, and duplicate measurements will be conducted where appropriate. All instruments used have been validated in prior clinical practice. Data collection forms are included in the protocol and managed through an EDC system.

Based on the actual number of participants enrolled in the 2 groups, dropout and exclusion cases, as well as demographic and other baseline characteristics, corresponding efficacy and safety analyses will be conducted. Descriptive statistical analysis will be used, with qualitative indicators described as frequency tables, percentages, or proportions; quantitative indicators will be described as mean (SD), median (IQR), and minimum and maximum values.

For primary end points and clinical efficacy analysis, the main and sensitivity analyses will be performed according to the full analysis set and per-protocol set, respectively. Safety analysis will be conducted using the safety set. The main analysis of the primary end point will use the log-rank test to compare the 2-year progression rates between groups, with Cox regression adjusting for covariates (eg, center) as a sensitivity analysis. Subgroup analyses will be conducted based on the center and whether >8 mm nodules were surgically removed. The malignancy risk index, quality-of-life scores at different time points, and other multiple measurement indicators will be analyzed using mixed-effects models. Eligibility-related protocol deviations, including any deviations from the retained immune disease exclusion criterion, will be documented. Participants with major eligibility deviations will be handled according to the prespecified analysis-set definitions, with sensitivity analysis based on the per-protocol set. Safety end points will summarize adverse reactions and events occurring during the study and compare rates between groups. Hypothesis testing will uniformly use 2-sided tests, providing test statistics and corresponding *P* values, with *P*<.05 considered statistically significant.

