**Methods:**

Adults aged 18 to 80 years with single or multiple mixed ground-glass nodules measuring ≤8 mm will be randomized in a 1:1 ratio to receive YFSJ optimized formula granules or matched placebo granules, 2 packets twice daily for 6 months. Both groups will receive guideline-based computed tomography surveillance and any clinically indicated standard diagnostic or therapeutic care. The primary outcome is the 2-year pulmonary nodule progression rate, defined as an increase in the lesion’s longest diameter of ≥2 mm, an increase in the solid component of ≥1 mm, or the appearance of a new solid component. Secondary outcomes include lung cancer detection rate, surgery rate, 6-month nodule size and volume change, artificial intelligence–based malignancy risk index, traditional Chinese medicine symptom score, Hospital Anxiety and Depression Scale (HADS) score, Pittsburgh Sleep Quality Index (PSQI) score, safety indicators, and exploratory plasma biomarkers. The primary analysis will use the full analysis set, Kaplan-Meier estimates, log-rank testing, and Cox regression adjusted for center and key covariates; repeated outcomes will be analyzed using mixed-effects models.

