### Case Selection

#### Sample Size Estimation

This trial uses the 2-year disease progression rate of pulmonary nodules as the primary end point. Previous studies have reported a 2-year progression rate of ≤8 mm mixed ground-glass nodules at approximately 24% [19]. Assuming a 2-year progression rate of 14% in the intervention group, with 80% power, a 5% false-positive error rate (2-sided), and a dropout rate controlled within 20%, a total of 596 participants need to be enrolled. The trial will include 600 patients, with 300 in the experimental group and 300 in the control group (Figure 1).

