#### YFSJ Optimized Formula Granules

Participants allocated to the experimental group will take optimized YFSJ formula granules—2 packets per dose, dissolved in hot water—twice daily for 6 months. The source formula is composed of 8 herbs as described in Table 1; the crude-drug equivalent dose and the final granule extraction ratio or packet weight should be verified against the investigational product specification.

**Table 1. T1:** Composition of the Yifei Sanjie Pill (YFSJ) source formula^a^.

Number	Herbal component	Latin or pharmaceutical name	Crude-drug equivalent in source formula, g
1	Sarcandra glabra	*Sarcandra glabra* (Thunb.) Nakai	15
2	Bombyx batryticatus	Bombyx batryticatus	10
3	*Ranunculus ternatus*	*Ranunculus ternatus* Thunb.	30
4	*Iphigenia indica*	*Iphigenia indica* Kunth	15
5	Fritillaria bulb	Bulbus *Fritillariae thunbergii*	15
6	*Pinellia ternata*	*Pinellia ternata* (Thunb.) Breit.	15
7	*Ganoderma lucidum*	*Ganoderma lucidum* (Leyss. ex Fr.) Karst.	30
8	American ginseng	*Panax quinquefolius* L.	15

a The investigational granules are manufactured by Jiangyin Tianjiang Pharmaceutical Co, Ltd. The batch number, quality-control fingerprint, heavy metal or pesticide testing, granule extraction ratio, and gram weight per packet will be recorded in the trial master file.

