#### Primary End Point

The primary outcome is the 2-year lung nodule progression rate. Progression of a ground-glass nodule is defined as an increase in the longest diameter of the lesion by ≥2 mm, an increase in the solid component by ≥1 mm, or the appearance of a new solid component. When multiple nodules are present, the largest or clinically dominant nodule will be used for primary assessment, and changes in other nodules will be documented as supportive information.

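### The log-rank test is described as comparing 2-year progression rates, which it does not do; keep the test, describe it correctly, and rest any 2-year-rate claim on the month-24 Kaplan-Meier difference

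*Protocol article*

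**What the plan says.** The target is a fixed-time quantity throughout the protocol article. The Primary End Point section reads "The primary outcome is the 2-year lung nodule progression rate". The last paragraph of the Introduction and the opening of the Discussion state the hypothesis as a reduction in that rate. Sample Size Estimation takes a control rate of about 24% from earlier studies and continues "Assuming a 2-year progression rate of 14% in the intervention group", concluding that "a total of 596 participants need to be enrolled".

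The Statistical Analysis section then assigns the test: "The main analysis of the primary end point will use the log-rank test to compare the 2-year progression rates between groups". The Abstract is a little wider: "The primary analysis will use the full analysis set, Kaplan-Meier estimates, log-rank testing, and Cox regression adjusted for center and key covariates". Kaplan-Meier estimates are therefore planned, but no section says which comparison of the month-24 estimates carries the 2-year claim, and none states a proportional-hazards assumption linking the test to that claim.

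Study drug is taken "twice daily for 6 months". Table 2 schedules chest CT at months 6, 12, 18 and 24, so 18 of the 24 months of follow-up are off treatment.

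**The concern.** The log-rank statistic sums observed minus expected events over all event times. It tests whether the two progression curves are the same, and no part of it singles out the cumulative proportion at month 24. Under proportional hazards the distinction has no practical effect, because curves that differ anywhere also differ at month 24 in the same direction. Here the drug is given for the first quarter of follow-up only, so the hazard ratio may well change over time.

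At stake is the sentence the trial will be able to write. Delayed progression and a lower 2-year progression rate are different findings for a trial about prevention. As worded, a significant log-rank P value would be read as establishing the second when the data might support only the first. In the other direction, a true 2-year difference that emerges late would be detected less often than planned.

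**Working it through.** **1. The plan's own figure.** Inputs from Sample Size Estimation: 24% versus 14%, 80% power, two-sided 5%, 20% dropout. Two-proportion formula with unpooled variance:

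n = (1.960 + 0.842)² × (0.24 × 0.76 + 0.14 × 0.86) / 0.10² = 7.849 × (0.1824 + 0.1204) / 0.01 = 237.7, so 238 per arm.

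238 / 0.8 = 297.5, so 298 per arm and 596 in total. This matches the stated number exactly.

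**2. Would a log-rank calculation need a different size?** Under proportional hazards the implied hazard ratio is ln(0.86)/ln(0.76) = 0.550, and the mean event proportion is (0.24 + 0.14)/2 = 0.19.

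- Schoenfeld: 88 events; 88 / 0.19 / 0.8 ≈ 579 participants.
- Freedman: 93 events; 93 / 0.19 / 0.8 ≈ 612 participants.

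Both lie within 3% of 596. The number was evidently derived for a fixed-time comparison, but it serves either analysis.

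**3. How the two comparisons behave.** Simulation settings: 300 per arm, events recorded at the CT visits of months 6, 12, 18 and 24, 20% independent dropout spread over 24 months, 20,000 runs per scenario, two-sided 5%. The comparator is the difference in month-24 Kaplan-Meier progression with Greenwood variance. Simulation error is small: the standard error is √(0.05 × 0.95 / 20,000) = 0.15 points near 5%. The control arm has a constant hazard reaching 24%, that is 6.6/12.8/18.6/24.0% at the four visits. The document gives only the month-24 rates, so every non-proportional shape below is an assumption.

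| Scenario (treatment-arm cumulative progression at months 6/12/18/24) | Log-rank rejects | Month-24 difference rejects |
|---|---|---|
| Identical curves | 4.9% | 4.9% |
| Proportional hazards, 24% vs 14% | 83.7% | 83.2% |
| Delay only, 3/8/15/24% | 6.2% | 5.1% |
| Delay only, 2/6/14/24% | 7.8% | 5.1% |
| Delay only, 0/3/10/24% | 12.7% | 5.1% |
| Late separation, 6.6/12.8/13.5/14% | 73.4% | 84.3% |
| Worse at month 6, then better, 9/12/13/14% | 71.6% | 84.1% |
| Early effect, 0/3/8.5/14% | 91.4% | 82.7% |
| Waning, interval hazard ratios 0.15/0.35/0.7/1.0 (24% vs 14%) | 90.8% | 82.7% |
| Waning, interval hazard ratios 0.1/0.5/0.8/1.0 (24% vs 15.2%) | 82.7% | 71.6% |

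In the three delay-only rows the log-rank rejections that favour treatment are 5.2%, 7.2% and 12.3%, against a nominal 2.5%; for the month-24 difference they are 2.6% to 2.7%.

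**4. Reading the table.** With identical curves or proportional hazards the two comparisons agree. With equal 2-year rates and delay, the log-rank test rejects more often than 5%. With late separation it loses about 11 points (84.3 − 73.4 = 10.9). With a waning effect it gains 8.1 points (90.8 − 82.7) or 11.1 points (82.7 − 71.6).

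**The case against.** The strongest reply is that this is a conventional time-to-event design in shorthand. Follow-up ends at progression, surgery, withdrawal, death or loss (Follow-Up and Data Collection), and surgery without progression is censored (Termination or Withdrawal Criteria). Kaplan-Meier with a log-rank test is a natural choice for such data, and the Abstract already lists Kaplan-Meier estimates, so a reader would see the two month-24 rates beside the P value. Interval details may sit in an analysis plan that is not shown.

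Most of this stands, and it rules out several stronger readings that a reader might infer:

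- *That the log-rank test is invalid or inflates the type I error.* It rejects in 4.9% of trials when the curves are identical. In the delay-only rows the curves do differ, so the rejection detects something real. Only the inference to the 2-year rate is unsupported.
- *That the trial is wrongly sized.* Step 2 of the working shows that 596 suits either analysis.
- *That the primary test should be replaced by the month-24 difference.* That would gain power if separation comes late but lose 8 to 11 points if the effect wanes, and waning is the more natural pattern after 6 months of drug. It is a trade-off between legitimate tests, and the documents do not settle it.
- *That leaving out a confidence interval is itself a defect.* A condensed article may leave that to the analysis plan.

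The reply does not reach the sentence in the Statistical Analysis section. It states what the test compares, and the statement is wrong for the quantity that the endpoint, the hypothesis and the sample size all name.

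**Conclusion.** The point holds as a misdescription with a real but limited consequence. The log-rank test compares progression curves over 2 years, while the protocol's claim concerns the rate at 2 years. The two coincide under identical curves or roughly proportional hazards, and a treatment confined to the first 6 of 24 months gives no assurance of that.

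Under the design assumption nothing is lost: power is about 84% for the log-rank test and 83% for the month-24 difference. If treatment only delays progression to the same 24%, the log-rank test rejects in about 6% to 8% of trials for moderate delay, and in about 13% when no progression at all occurs on treatment in the first 6 months. If a true 24% versus 14% difference separates only after month 12, its power is 73% against 84%. These departures rest on assumed curve shapes, on independent dropout of 20%, and, for delay only, on curves that meet exactly at month 24. The correction is worth making because it costs almost nothing and stops a delay-only result from being reported as a lower 2-year rate. It is no reason to abandon the planned test.

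**What to change.** In the Statistical Analysis section:

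1. Keep the log-rank test as the primary test, and describe it as comparing time to progression over 2 years between the groups.
2. Name the between-arm difference in Kaplan-Meier cumulative progression at the month-24 visit, with its 95% CI, in the full analysis set, as the primary effect estimate.
3. State that any conclusion that treatment reduces the 2-year progression rate rests on that difference and its CI, and not on the log-rank P value alone.

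The cost is wording only, with no new data and no loss of power for the primary test. The Results section plans database lock for early 2028 and reports no comparative efficacy results, so the change can be made before unblinding; afterwards it could look data-driven. There is one downside to accept in advance. A significant log-rank result may come with a month-24 interval that includes zero, and then only a claim about time to progression is supported. In the two waning examples the net gap in power, 8 to 11 points, indicates how often this could matter.

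### The Abstract counts covariate-adjusted Cox regression as part of the primary analysis, while the Statistical Analysis section makes it a sensitivity analysis behind the log-rank test and leaves its analysis set unclear

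*Protocol article*

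**What the plan says.** The Methods paragraph of the Abstract states: "The primary analysis will use the full analysis set, Kaplan-Meier estimates, log-rank testing, and Cox regression adjusted for center and key covariates". Adjusted Cox therefore sits inside the primary analysis, on the full analysis set, beside the log-rank test.

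The Statistical Analysis section gives a different hierarchy. "The main analysis of the primary end point will use the log-rank test to compare the 2-year progression rates between groups", and the sentence continues "with Cox regression adjusting for covariates (eg, center) as a sensitivity analysis". No stratification or covariate is named for the log-rank test, so the plain reading is an unadjusted test.

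Earlier in the same paragraph the analysis sets are assigned: "the main and sensitivity analyses will be performed according to the full analysis set and per-protocol set, respectively". A later sentence again links sensitivity analysis to the per-protocol set.

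The sample size rests on 2-year progression of about 24% in controls and 14% with YFSJ, 80% power, 2-sided 5% and up to 20% dropout, and concludes that "a total of 596 participants need to be enrolled".

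**The concern.** A model cannot be both part of the primary analysis and a sensitivity analysis to it. Both texts are current and neither is a record of superseded wording. Any analysis plan that follows one of them contradicts the other.

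Three things are at stake. First, if log-rank and adjusted Cox fall on opposite sides of P=.05, a reader could not tell from the article which was meant to decide the trial. Second, the Cox model could be run on the full analysis set (Abstract) or the per-protocol set (a literal reading of the Statistical Analysis section). Third, the endpoint and sample size concern the 24-month rate, but no between-group difference in that rate is named as the effect estimate; a log-rank test compares hazards across follow-up and yields no such difference.

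**Working it through.** **1. Which text does the sample size support?** Inputs from Sample Size Estimation: p1 = 0.24, p2 = 0.14, 2-sided alpha 0.05, power 80%, dropout 20%.

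- Unpooled two-proportion formula: n = (1.960 + 0.842)² × (0.24×0.76 + 0.14×0.86) / 0.10² = 7.849 × 0.3028 / 0.01 = 237.7, so 238 per arm.
- Dropout: 238 / 0.80 = 297.5, so 298 per arm and 596 in total. This is the stated figure exactly.

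The plan is sized for an unadjusted comparison, which fits the Statistical Analysis section.

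**2. Is the log-rank test compatible with that size?** Under proportional hazards, HR = ln(0.86)/ln(0.76) = 0.55. With 600 enrolled and 20% lost, 240 per arm remain and 240 × (0.24 + 0.14) = 91 events are expected. Power is 81.6% (Schoenfeld), against 79.9% for two proportions. The two agree closely.

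**3. What does the ambiguity cost?** Simulation, 1,500 trials per setting. Assumptions not in the documents: 600 participants, 5 centers, one standard normal prognostic covariate with the log-HR per SD shown, center SD 0 to 0.3, about 20% censoring over 2 years, and conditional treatment HR 0.55 under the alternative. CT at months 6, 12, 18 and 24 follows the schedule table. Monte Carlo error is about 0.6 points near 5% and 1 point near 80%.

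| Covariate log-HR per SD (center SD) | Null: log-rank | Null: Cox | Null: either | Effect: log-rank | Effect: Cox | Effect: tests disagree |
|---|---|---|---|---|---|---|
| 0 (0) | 5.0% | 5.1% | 5.4% | 84.3% | 84.0% | 2.3% |
| 0.5 (0.2) | 6.0% | 6.1% | 7.2% | 80.6% | 82.1% | 5.7% |
| 0.8 (0.3) | 5.7% | 5.1% | 7.8% | 78.9% | 85.5% | 10.1% |
| 1.2 (0.3) | 4.3% | 4.8% | 7.1% | 72.5% | 84.2% | 15.7% |

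Each test alone stays near 5%. Claiming success on either gives 5.4% to 7.8%. Measured against the log-rank test in the same simulated trials, the excess is 0.4, 1.2, 2.1 and 2.8 points. Two independent tests would give 1 − 0.95² = 9.75%; these are strongly correlated, so that ceiling does not apply.

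**4. What might adjustment gain?** In the table, Cox minus log-rank power is −0.3, 1.5, 6.5 and 11.7 points. The upper end is generous. The conditional HR was held at 0.55, so with a strong covariate the marginal progression rate under treatment lies above 14% and the unadjusted test faces a smaller effect than planned. A second simulation set the arm rates at 24% and 14%, with covariate HRs of 1.5, 2.0 and 2.5 per SD. Power went from 83.7% to 84.1%, 83.5% to 86.5% and 85.7% to 90.3%, gains of 0.4, 3.0 and 4.6 points. Its either-test false-positive rates were 5.6%, 7.1% and 7.2%, in line with step 3.

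**The case against.** The strongest reply is that the Statistical Analysis section governs and is clear: it names one main test, the sample size matches it, and the Abstract merely compresses three methods into one sentence. On that view only an abstract needs rewording. Much of this stands. The log-rank test keeps its 5% level, and inflation arises only if someone sets the section aside and takes the better result. The lowest simulated figure, 5.4%, cannot be told from 5% at this number of replicates, and no document gives the strength of any covariate.

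The reply does not remove the conflict. The Abstract says in terms what the primary analysis will use, and the analysis set for Cox is uncertain within the Statistical Analysis section itself.

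Two stronger inferences are not supported:

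- A reader might infer that adjusted Cox would never be run on the full analysis set. That is one of two readings. The Abstract places it there, and the sentence assigning analysis sets may concern populations only, with Cox a separate, model-based sensitivity analysis.
- A reader might infer that the planned 10-point effect is never estimated. The Abstract plans Kaplan-Meier estimates, which give 24-month progression by arm. What is not named is the difference between arms with its interval.

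**Conclusion.** The inconsistency is real and concerns which result decides the trial. Its size is modest: a false-positive rate of about 5.4% to 7.8% if either result could be claimed, and disagreement between the tests in roughly 2% to 16% of trials under the planned effect. Both ranges depend on assumed covariate strengths, and the first also on someone choosing the better result.

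A reader might go further and conclude that the trial's type I error is not 5%, or that an unadjusted main test is a mistake. The documents support neither. The unadjusted log-rank test is valid in a randomized trial, no stratified randomization is described that it would have to reflect, and 596 reproduces exactly on an unadjusted basis. Lack of adjustment is a question of efficiency, worth from about nothing to several points of power depending on how prognostic baseline nodule size is. The Abstract's key covariates may be listed in the analysis plan, so their absence from the article is not part of this point.

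**What to change.** Before unblinding, state the same single primary test, effect estimate and analysis set in the Abstract and in the Statistical Analysis section. Two options resolve the conflict:

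- **Keep the log-rank test** on the full analysis set as primary, which matches the sample-size basis. Correct the Abstract, and name the adjusted Cox model on the full analysis set as a sensitivity analysis.
- **Preferably for precision, make adjusted Cox primary:** one Cox model on the full analysis set, adjusted for center, baseline longest diameter and baseline solid-component size, with its treatment P value as the only primary test. The unadjusted log-rank test becomes a sensitivity analysis.

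Under either option, label the per-protocol repeat as its own sensitivity analysis, and report the Kaplan-Meier difference in 24-month progression with a 95% CI.

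The cost is wording in the protocol and analysis plan. No new data are needed, since baseline CT is scheduled for every participant, and the enrollment target does not change. The second option has one small drawback: its hazard ratio is conditional on the covariates rather than marginal. Statisticians stay blinded until database lock, planned for early 2028, so the choice can still be made without knowledge of the results.

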The purpose of this multicenter, randomized, double-blind, and placebo-controlled trial is to evaluate whether YFSJ, administered for 6 months in addition to guideline-based surveillance, reduces the 2-year progression rate of high-risk pulmonary nodules compared with placebo plus the same surveillance strategy. We hypothesize that YFSJ will reduce nodule progression without increasing clinically meaningful adverse events and will improve selected TCM symptoms, psychological distress, sleep quality, and exploratory plasma biomarkers related to phlegm-heat-toxin pathogenesis.

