#### Safety Outcomes

The following safety outcomes will be assessed throughout the study:

Vital signs, including pulse, respiratory rate, blood pressure, and temperatureBlood routine, liver function, kidney function, urinalysis, stool examination, and electrocardiogram ()All adverse events and serious adverse events, including onset date, duration, severity, relationship to study medication, action taken, outcome, and whether unblinding was required

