### Follow-Up and Data Collection

Baseline data will include demographics, smoking history, comorbidities, prior cancer history, medication history, physical examination, vital signs, blood routine, liver function, kidney function, urinalysis, stool examination, tumor markers, ECG, chest CT, AI-derived nodule variables, TCM symptom score, HADS, and PSQI. Follow-up visits will occur at 3 and 6 months during the intervention period and every 6 months thereafter until nodule progression, surgery, withdrawal, death, loss to follow-up, or study completion. The trial protocol is version 3.0 (March 20, 2023), and the schedule of study procedures is shown in Table 2.

**Table 2. T2:** Schedule of study procedures, assessments, and follow-up visits.

Procedure	Screening/baseline	Randomization	Month 3	Month 6	Month 12	Month 18	Month 24/ end point
Eligibility	✓						
Consent	✓						
Demog.^a^	✓						
Random.^b^		✓					
Study drug		Start	Continue	End			
Meds^c^	✓	✓	✓	✓	✓	✓	✓
Vitals or AEs^d^	✓		✓	✓	✓	✓	✓
Labs or ECG^e^	✓		✓	✓	As indicated	As indicated	✓
CT^f^	✓			✓	✓	✓	✓
AI^g^	✓			✓	✓	✓	✓
TCM^h^ symptoms	✓		✓	✓	✓	✓	✓
HADS^i^ or PSQI^j^	✓		✓	✓	✓	✓	✓
Plasma	✓			✓			Optional or if specified
End point							✓

a Demog.: demographics and medical history.

b Random.: randomization and dispensing.

c Meds: concomitant medication review.

d AEs: adverse events.

e ECG: electrocardiogram.

f CT: computed tomography.

g AI: artificial intelligence.

h TCM: traditional Chinese medicine.

i HADS: Hospital Anxiety and Depression Scale.

j PSQI: Pittsburgh Sleep Quality Index.

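### The only stated safety comparison pools 6 months on drug with up to 18 months off drug, which can dilute an on-drug excess of common adverse events

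*Protocol article*

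**What the plan says.** Both arms take granules for the same period. The active-arm text reads "2 packets per dose, dissolved in hot water—twice daily for 6 months", the placebo text gives the same duration, and Table 2 ends study drug at month 6.

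Safety collection runs much longer. Safety Outcomes states: "The following safety outcomes will be assessed throughout the study". Table 2 has adverse events at months 3, 6, 12, 18 and 24. After month 6, visits continue "every 6 months thereafter until nodule progression, surgery, withdrawal, death, loss to follow-up, or study completion".

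The comparison is set out in one sentence of Statistical Analysis: "Safety end points will summarize adverse reactions and events occurring during the study and compare rates between groups". It uses the safety set, and tests are two-sided at 5%. No on-treatment or treatment-emergent window is named. Safety Outcomes does record what such a window would need: "All adverse events and serious adverse events, including onset date, duration, severity, relationship to study medication".

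The result carries weight. The Introduction says: "We hypothesize that YFSJ will reduce nodule progression without increasing clinically meaningful adverse events". The Discussion makes the role of YFSJ as an adjunctive option conditional on adverse events not increasing. No safety margin is given.

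**The concern.** The stated window is up to four times as long as the dosing period. Once dosing stops, and absent delayed effects, both arms accrue events such as infections, raised laboratory values and gastrointestinal complaints at the same background rate. A comparison over the whole study adds those events to both arms, so the ratio moves towards 1 and the noise grows.

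Dilution matters more here than in a trial where safety is only described. The hypothesis is an absence of increase, the test is an ordinary two-sided one, and no margin is set. A non-significant difference is therefore easily read as no increase, and dilution works in favour of that reading. No independent data monitoring committee is planned and the statisticians stay blinded until database lock, so this final comparison is the only between-group look at safety that the article describes.

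**Working it through.** **The plan's own figure.** The article gives no figure for the safety comparison. Its only sample-size figure, 596, is for the primary end point, and it reproduces. With 24% vs 14%, two-sided 5% and 80% power, the unpooled formula gives 237.7, so 238 per arm; 238/0.8 = 297.5, so 298 per arm and 596 in total. The pooled formula gives 241 per arm, which becomes 302 per arm and 604 in total after 20% dropout. The planned 300 per arm is used below.

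**Inputs.** From the article: 6 months on drug, 24 months maximum follow-up, 300 per arm, two-sided 5%, and 2-year progression of 24% vs 14%. Assumed, because the article gives no adverse event rates: a background risk b per 6-month block, an on-drug risk t in the active arm, no excess after dosing stops, independent blocks, and full follow-up.

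**Cumulative risk.** Over 24 months, placebo = 1 − (1 − b)^4 and active = 1 − (1 − t)(1 − b)^3.

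- b = 10%, t = 20%: placebo 1 − 0.9^4 = 34.4%; active 1 − 0.8 × 0.9^3 = 41.7%. The ratio falls from 2.0 to 1.21.
- b = 5%, t = 10%: placebo 1 − 0.95^4 = 18.5%; active 1 − 0.9 × 0.95^3 = 22.8%. The ratio falls from 2.0 to 1.23.

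**Power.** Power = Φ[(d − 1.96·SE0)/SE1], where d is the difference, SE0 uses the pooled proportion and SE1 the separate ones.

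- 10% vs 20%: (0.100 − 1.96 × 0.02915)/0.02887 = 1.48, power 93%.
- 34.4% vs 41.7%: (0.0729 − 1.96 × 0.03964)/0.03953 = −0.12, power 45%.
- 5% vs 10%: power 64%. 18.5% vs 22.8%: power 25%.

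**Other assumed rates.** With a constant hazard multiplied only during dosing and 300 per arm:

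| Background 6-month risk | On-drug hazard ratio | Power, 6 months | Power, 24 months |
|---|---|---|---|
| 5% | 2.0 | 61% | 23% |
| 10% | 2.0 | 88% | 38% |
| 20% | 2.0 | 99% | 55% |
| 30% | 2.0 | >99% | 59% |
| 10% | 1.5 | 41% | 14% |

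The rate ratio over 24 months is (2 × 6 + 18)/24 = 1.25 for a doubled rate and (1.5 × 6 + 18)/24 = 1.125 for a ratio of 1.5.

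**Events that occur only on drug.** If 2% vs 8% have such an event during dosing and none occur later, the 24-month figures are still 2% vs 8% and power stays at 92%. Dilution needs a continuing background rate.

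**Unequal follow-up.** Visits stop at progression or surgery. With constant progression hazards giving 24% and 14% at 2 years, and progression detected at 6-monthly visits, mean follow-up is 6 × (1 + S(6) + S(12) + S(18)), where S(t) is the proportion still progression-free at month t:

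- placebo: 6 × (1 + 0.934 + 0.872 + 0.814) = 21.7 months
- YFSJ: 6 × (1 + 0.963 + 0.927 + 0.893) = 22.7 months

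With a 10% background risk per block and no drug effect, this alone gives 31.4% vs 32.7% with an event. The gap of 1.3 points runs against YFSJ.

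**The case against.** The strongest reply is about scope. One sentence in a journal article says which events are reported. It does not say that a single pooled table is the only analysis, and it leaves the type of rate undefined. Treatment-emergent windows are commonly set in the analysis plan, which is not shown. This stands in part: a reader might infer that no on-treatment analysis exists, and the article does not support that. What remains is that the one comparison it does state covers the whole study, so that sentence should be changed or brought into line with the plan.

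Second, the same sentence covers adverse reactions as well as events, and causality is recorded. This also stands: reactions confined to dosing are not diluted. It does not settle the matter, because causality is judged case by case and the Discussion's condition concerns adverse events as a whole.

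Third, capture is not constant over time. Table 2 schedules laboratory tests and ECG at months 3, 6 and 24 but only as indicated at months 12 and 18, and visits are closer together during dosing. Dilution could therefore be weaker than the equal-block model shows. That is a fair limit on the size. It is also a reason not to pool two periods with different surveillance.

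Fourth, whole-study reporting can reveal delayed effects. That is right, and is why the 24-month table should be kept.

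A reader might also infer that the early end of follow-up seriously biases the comparison. On the article's own progression rates it does not: the imbalance is about one month, and it would make YFSJ look slightly worse.

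**Conclusion.** The concern holds as a risk in the comparison as stated. Study drug covers 6 of up to 24 months, and pooling the whole period can dilute an on-drug excess of all-cause events that have a continuing background rate. In the illustration a doubled risk shrinks to a ratio of 1.21, and power falls from 93% to 45%. Power fell in every scenario in the table (background 5% to 30%, hazard ratio 1.5 to 2.0).

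These sizes rest on assumed event rates, no excess after dosing, constant capture and full follow-up. Eighteen months off drug is a maximum. Allowing for follow-up that ends at progression barely changes the dilution: with 22.7 months in the active arm, a doubled rate gives (12 + 16.7)/22.7 = 1.26 instead of 1.25.

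It would go too far to say that the plan hides harm or will produce a false safety conclusion. The true event rates are unknown, adverse reactions are summarised too, and the recorded onset dates allow the right comparison to be made. The point is worth correcting before database lock, because an on-treatment split chosen after unblinding would be post hoc.

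**What to change.** State in Statistical Analysis that the main between-group safety comparison is of events with onset from first dose to end of treatment plus a short lag, whose length is fixed before unblinding. Without a lag, a reaction starting just after the last dose would be counted as off-treatment.

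Report later events in a separate off-treatment table, per person-year, because follow-up ends at progression or surgery. Keep the whole-study table as supportive, for delayed effects. Give the difference with its confidence interval, and say that a non-significant result will not by itself be read as no increase.

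The cost is one sentence on the window and one table split. No new data are needed, since the record already covers each event "including onset date, duration, severity, relationship to study medication, action taken, outcome, and whether unblinding was required". Database lock is planned for early 2028, so there is time. The one trade-off is that the pooled 24-month table is no longer the lead safety result. If the analysis plan already defines such a window, the article's sentence only needs to be aligned with it.
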